### Outcome measurements

The primary outcome is defined as the percentage change of proteinuria in all three groups after 6 months of intervention. Secondary outcomes include the changes in urinary protein creatinine ratio (UPCR), eGFR, and serum Gd-IgA1 levels in all three groups from baseline. The clinical characteristics of the patients will be collected at baseline before enrollment, including age, sex, age, course of the disease, combined disease, medication history, and so on. Throughout the follow-up, patients will be asked to provide urine and blood samples, which will be collected independently at visit 4 and visit 8, which will be collected for the following: collection, storage, and distribution of biological samples and related data for scientific research in the biobank of Dongzhimen hospital. In order to assess drug compliance, participants will be checked for the remaining number of drugs at each follow-up visit. Patient compliance will be calculated as the percentage of the actually taken number of tablets (distributed pills − returned pills) to the distributed number of drugs.

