### Sample size

This is a double-blind, randomized, three-group-parallel, placebo-controlled clinical study, and the sample size estimates were based on the change in proteinuria levels. According to the study results when using similar types of drugs (HCQ) for the treatment of IgA nephropathy [12, 25], the average baseline proteinuria was 2.0±0.8 g/day, and 36 participants in each arm could provide 90% of the detection ability, assuming that the placebo group level of proteinuria had not changed, and the ART treatment detected a 25% reduction in proteinuria (ART group: 0.5±0.5 g/day). Assuming that the two doses of the ART group has the same efficacy (the ratio of the ART group to the placebo group is 2:1), and a 10% dropout rate with a type I error rate of 0.05, we plan to enroll 120 participants (40 in each group) in the study.

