### Statistical analysis

All results will be analyzed based on an intention-to-treat (ITT) analysis. Normally distributed data will be expressed as the mean ± standard deviation (SD), while nonnormally distributed data will be expressed as the median of the interquartile interval (IQR). Categorical data will be summarized as counts and percentages. The Shapiro-Wilk test will be performed to determine the normal distribution of continuous variables. For the comparison of baseline characteristics between groups, continuous variables (standard normal distribution) will be analyzed by a one-way ANOVA, continuous variables (nonstandard normal distribution) and ordered categorical variables will be tested by the Kruskal-Wallis *H* test, and unordered categorical variables or count variables will be tested by the chi-square test and Fisher’s exact test.

For the effectiveness outcomes, the primary outcome of proteinuria will be described by the percentage change of 24-h proteinuria test results at each visit from baseline, and the secondary outcomes of UPCR and eGFR will be described by the mean difference between the test results of each visit and the baseline. A paired-samples *t*-test or the Wilcoxon signed-rank test will be used for comparisons within groups at each visit time point from baseline, and one-factor ANOVA and the Kruskal-Wallis *H* test will be used for comparisons among groups at each visit time point.

For the safety indicators, adverse events will be described according to the number of cases and percentage, and the chi-square test and Fisher’s exact test will be used to analyze the differences between groups. The missing values will be filled up by the last-observation-carried-forward method. For the initial analysis, we will not adjust for confounders or stratification, and for the secondary analysis, we will adjust for confounders for subgroup analyses, such as baseline proteinuria (3 g/day), renal function (eGFR 45 m1/min per 1.73 m^2^), blood pressure level (systolic blood pressure 140 mmHg), MEST-C classification [26], and the new international risk-prediction score [27]. SAS 9.4 (SAS Institute Inc.) will be used as the statistical analysis tool. A 2-sided *P* < 0.05 will be defined as statistically significant.

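### Last observation carried forward fills the 6-month primary outcome with values at least 3 months old, which can bias the contrast in either direction

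*Protocol article*

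**What the plan says.** The Statistical analysis section gives one rule for missing data: "The missing values will be filled up by the last-observation-carried-forward method". The sentence stands in the paragraph on safety indicators, but its wording is general. The same section says "All results will be analyzed based on an intention-to-treat (ITT) analysis".

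Under Outcome measurements, "The primary outcome is defined as the percentage change of proteinuria in all three groups after 6 months of intervention". Groups are compared one time point at a time, by one-way ANOVA or by rank: "Kruskal-Wallis *H* test will be used for comparisons among groups at each visit time point". No repeated-measures model is named.

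Four other places bear on the point:

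- **Study design** puts the visits after randomization at months 1, 2, 3 and 6.
- **Sample size** allows for "a 10% dropout rate with a type I error rate of 0.05".
- **Withdrawal criteria** keep patients who stop treatment on the visit schedule, but name only end-point events and safety data as what must be recorded.
- **Termination criteria** take patients out of the study for liver or kidney damage, severe drug-caused discomfort or severe drug allergy.

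**The concern.** Carrying the last value forward assumes that a patient's proteinuria stays where it was at the last visit. In this schedule that visit lies at least half the treatment period before the endpoint.

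A patient lost early contributes a value close to baseline, which hides any later change. A patient lost at month 3 while on drug contributes an on-treatment value as a 6-month result, even if the benefit went when treatment stopped. The first pattern shrinks the effect and the second inflates it, so the rule cannot be defended as conservative.

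Some of the removal grounds are harms of the drug, so loss may differ between artesunate and placebo. In that case a trend common to all arms can turn into a spurious difference. What is at stake is the estimate and test for the primary outcome.

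**Working it through.** **Inputs from the protocol article.** Baseline 2.0 g/day; planned reduction 25%, that is 0.25 × 2.0 = 0.5 g/day; placebo unchanged; 36 per arm for 90% power; dropout 10% (all Sample size). Visits at months 1, 2, 3 and 6 (Study design).

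**Assumptions not in the article.** Dropout by arm, and *f*, the share of the 6-month effect already present at the last observed visit. Both are shown as ranges.

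**1. The plan's own figures.** 36 / (1 − 0.10) = 40 per arm and 3 × 40 = 120, as stated. The plan therefore expects about 4 losses per arm, 12 in all. With SDs of 0.8 (placebo) and 0.5 (artesunate) at 1:1, n = (0.64 + 0.25) × (1.960 + 1.282)² / 0.5² = 37.4, so 38 per arm; power at 36 is 0.889. That is close to the stated 36 and 90%.

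**2. Age of the carried value.** 6 − 3 = 3 months at best, 4 or 5 months if the last visit was month 2 or 1. If no later value exists and baseline is carried, the change is 0%.

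**3. Effect still building at the last visit.** With a flat placebo arm only the artesunate dropout *d* matters:

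target = (1 − d) × 25 + d × f × 25

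| Dropout, placebo / artesunate | f = 0 | f = 0.5 | f = 1 |
|---|---|---|---|
| 10% / 10% | 22.5 | 23.75 | 25 |
| 5% / 15% | 21.25 | 23.1 | 25 |
| 0% / 20% | 20.0 | 22.5 | 25 |

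The shortfall is 0 to 2.5 points (up to 10% of the effect) at equal 10% dropout, and up to 5 points (20%) in the last row.

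**4. Benefit lost on stopping.** Suppose every artesunate patient who leaves had the full effect at the last visit and none at month 6. The all-randomised effect is (1 − d) × 25 + d × 0: 22.5 points at d = 10% and 20.0 at d = 20%. Carrying on-drug values forward gives 25 both times, an overstatement of 2.5 and 5 points.

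**5. Simulation.** 6,000 runs per scenario, in g/day, assuming SD of change 0.667, within-patient correlation 0.6, linear onset and uniform dropout timing. The standard error with no dropout, 0.129, equals 0.667 × √(1/40 + 1/80), so these runs correspond to pooled artesunate (80) against placebo (40).

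- True effect −0.5, dropout 10% in each arm: carried forward −0.462, observed cases −0.499.
- No true difference:

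| Common trend in all arms | Dropout, placebo / artesunate | False difference | Type I error |
|---|---|---|---|
| Fall of 0.5 | 10% / 10% | +0.002 | 4.9% |
| Fall of 0.5 | 5% / 20% | +0.057 | 7.4% |
| Rise of 0.2 | 5% / 20% | −0.023 | 5.6% |

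A positive difference counts against artesunate and a negative one favours it. With equal dropout and no true effect, the bias is essentially nil.

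**The case against.** **Size and setting.** At the planned dropout, split equally, the bias is at most a tenth of the effect. It disappears if proteinuria has plateaued by the last visit, or if there is no true difference and dropout is equal. The Discussion calls the trial a proof-of-concept study. All of this stands and limits the severity.

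**Stopping treatment is not the same as missing data.** The Withdrawal criteria keep such patients on scheduled visits, so their month-6 value may exist. This stands in part: proteinuria is not clearly among the items to be recorded, and patients removed under the Termination criteria are a separate group.

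**Scope and silence.** The rule sits in a safety paragraph, and sensitivity analyses are commonly left to an analysis plan that is not shown. Their absence is therefore no fault here. The choice of method is stated, however, and no other rule in the article could serve the primary analysis.

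Three stronger readings are tempting and are not supported:

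- *The standard error is about 5% too small and confidence intervals are too narrow.* √(36/40) = 0.949 only compares sample counts. In simulation with values missing completely at random, the model standard error matched the estimator's own sampling SD (0.1285 against 0.1282). The section names tests and P values, not confidence intervals.
- *Leaving will differ by arm.* Acute kidney injury and raised transaminases can occur on placebo too. The text supports only that it may differ.
- *A mixed model alone cures the problem.* In step 4, a model that assumes data missing at random sees only on-drug values from those who leave and would also return about 25 points.

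**Conclusion.** The concern holds as a fault in a stated method, at the level of should-fix. Filling missing 6-month proteinuria with a value at least 3 months old biases the primary contrast except in the two situations conceded above.

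In the scenarios examined, the distortion is 0 to 2.5 of 25 points at the planned 10% dropout and up to 5 points at 20% artesunate dropout. It runs toward no effect if the effect is still building, and toward too large an effect if benefit is lost on stopping. With no true difference, unequal dropout and a common trend raised type I error to 7.4% in the worst case simulated.

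These sizes rest on assumed onset, offset and dropout by arm, none of which the article gives. The direction therefore cannot be known in advance. Bias is the harm; no claim about understated standard errors is made.

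**What to change.** Before unblinding:

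1. Replace the carried-forward rule for the primary outcome with a likelihood-based repeated-measures model, or multiple imputation, using all post-baseline proteinuria values. Take the month-6 between-arm contrast as the estimate. Table 1 is not shown, so month-2 collection is inferred from the analysis at each visit; the method works without it.
2. State that month-6 proteinuria is recorded at the visits already required after treatment stops, and include it in the intention-to-treat analysis.
3. Add a sensitivity analysis that imputes missing values for artesunate patients from the placebo arm. This covers benefit lost after stopping, which a missing-at-random model does not address.
4. Keep last observation carried forward at most as a further sensitivity analysis.

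The outcome scale and baseline adjustment are separate choices and need not change for this purpose. The cost is a little more analysis work: the visits are already scheduled and SAS is already the stated software. Changing the rule after unblinding would look data-driven.

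### The primary comparison of percentage change in proteinuria ignores baseline as a covariate and names two tests: valid, but possibly inefficient and not tied to one effect measure

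*Protocol article*

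**What the plan says.** In the Protocol article, Outcome measurements states: "The primary outcome is defined as the percentage change of proteinuria in all three groups after 6 months of intervention". Statistical analysis describes this outcome as the percentage change of the 24-h result from baseline. It names one-factor ANOVA and the Kruskal-Wallis test for comparing the arms at each visit, without saying which is primary.

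On adjustment, the same section says: "For the initial analysis, we will not adjust for confounders or stratification". A secondary analysis adjusts for confounders in subgroup analyses. Baseline proteinuria is listed there with a cut at 3 g/day.

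On normality it says: "The Shapiro-Wilk test will be performed to determine the normal distribution of continuous variables". A rule that sends non-normal variables to Kruskal-Wallis is written out only for baseline characteristics. Non-normal data are to be summarised by median and interquartile range.

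Sample size works in g/day, not in percentages: "the average baseline proteinuria was 2.0±0.8 g/day", no change on placebo, and "the ART treatment detected a 25% reduction in proteinuria (ART group: 0.5±0.5 g/day".

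**The concern.** Percentage change uses each patient's baseline as a divisor. That corrects for baseline by a fixed rule (slope 1 on the log scale) rather than by the slope the data support. Unless the two measurements are highly correlated, this over-corrects and carries baseline noise into the outcome. Percentage change is also bounded at -100% with a long right tail, so its arithmetic mean sits above the typical proportional change.

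Naming two tests leaves the effect measure open as well. ANOVA goes with a difference in means, while Kruskal-Wallis gives no between-arm estimate with a confidence interval. At stake are precision in a trial of 40 per arm and a clear headline estimate. The validity of the randomised comparison is not at stake.

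**Working it through.** **Inputs from the Protocol article.** Sample size: baseline 2.0 ± 0.8 g/day; reduction 25%, that is 0.5 ± 0.5 g/day; "36 participants in each arm could provide 90% of the detection ability"; "a 10% dropout rate with a type I error rate of 0.05". Statistical analysis: two-sided testing.

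**The plan's own figure.** With SD 0.8 in placebo, 0.5 in ART and equal arms, n = (0.8² + 0.5²)(1.960 + 1.282)²/0.5² = 0.89 × 10.51/0.25 = 37.4, so 38 per arm. Power at 36 is 88.9%. This is close to the stated 36 and 90%. Then 36/0.9 = 40 per arm, 120 in total. The figure rests on absolute change, so it does not give the power of the planned percentage-change test.

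**Assumptions not in the article.** Proteinuria is log-normal; log SD is equal at baseline and month 6; the true ratio is 0.75 on both doses; the log-scale correlation ρ between baseline and month 6 runs from 0.3 to 0.8.

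**Closed form, one dose v placebo, 36 per arm.**
- Log SD: σ = √ln(1 + (0.8/2.0)²) = 0.385. Effect: δ = −ln 0.75 = 0.288.
- Unadjusted log ratio: SD = σ√(2(1 − ρ)).
- ANCOVA: SD = σ√(1 − ρ²).
- Variance ratio, ANCOVA to unadjusted: (1 + ρ)/2.
- At ρ = 0.5 the unadjusted SD is 0.385 and its standard error 0.385 × √(2/36) = 0.091. Then 0.288/0.091 − 1.96 ≈ 1.21, giving 89% power. The ANCOVA SD is 0.334, giving 96%.

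| ρ | Variance ratio | Power, unadjusted v ANCOVA | n per arm for 90%, unadjusted v ANCOVA |
|---|---|---|---|
| 0.3 | 0.65 | 76% v 91% | 53 v 35 |
| 0.5 | 0.75 | 89% v 96% | 38 v 29 |
| 0.7 | 0.85 | 98% v 99% | 23 v 20 |

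**Simulation of the three-arm test** (2 degrees of freedom throughout, 36 per arm, 3,000 trials per scenario):

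| ρ | ANOVA, % change | Kruskal-Wallis, % change | ANOVA, log ratio | Log ANCOVA |
|---|---|---|---|---|
| 0.3 | 75% | 76% | 79% | 93% |
| 0.5 | 89% | 89% | 91% | 97% |
| 0.7 | 99% | 99% | 99% | 100% |
| 0.8 | 100% | 100% | 100% | 100% |

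Here most of the gain comes from the baseline covariate, not from taking logs. If the month-6 log SD is wider (0.6), the gain over Kruskal-Wallis shrinks: 49% v 56% (ρ 0.3), 64% v 67% (0.5), 81% v 83% (0.7) and 92% v 94% (0.8).

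**Effect measure.** With no true change, the placebo mean percentage change is 100(exp(s²/2) − 1), where s = σ√(2(1 − ρ)). At ρ = 0.5 this is +7.7%; a true 25% fall appears as an ART mean of −19.2%, and the contrast is −26.9 points. At ρ = 0.3 the three values are +10.9%, −16.8% and −27.7; at ρ = 0.8 they are +3.0%, −22.7% and −25.8.

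**Choice of test.** In simulations with no effect, letting Shapiro-Wilk choose between the two tests kept type I error at 4.5% to 5.2%. With a true effect, power stayed within 1 point of ANOVA or rose by up to 3. Running both tests and taking the smaller p gave 5.8% to 7.4%.

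**The case against.** The strongest reply is that an unadjusted randomised comparison is valid for its own target, so this is a preference about efficiency. That stands.

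The size of the gain also depends on a correlation that the article does not report. The only SD attached to a change is the 0.5 g/day for ART; in this model that corresponds to ρ of about 0.8, where nothing is gained. However, the stated 36 per arm is approached only by also using the baseline SD of 0.8, and a placebo change SD of about 0.8 corresponds to ρ of about 0.5. The article therefore does not settle the matter. The eligibility floor of 1.0 g/day may reduce the skew too. If it also held at randomisation (an assumption), power at ρ = 0.5 would be 91% v 96% and the placebo shift about +5%.

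A reader might infer three stronger things, and the article supports none of them:
- **That the reported effect is seriously misstated.** Arm means shift, but with equal log SDs the contrast is only about 1 to 3 points from 25 (up to about 5 with the wider month-6 spread). At ρ = 0.5 the ratio of arm means, 0.808/1.077, is still 0.75. The planned medians for skewed data largely avoid the shift.
- **That a Shapiro-Wilk switch decides the primary test and costs power.** The switch is stated only for baseline characteristics, and the simulation shows no power cost.
- **That baseline is discarded.** It is the divisor of the outcome, and it reappears in the secondary subgroup analyses.

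Which of the two tests is primary may be settled in an analysis plan not shown. The refusal to adjust, by contrast, is a positive statement in the article.

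**Conclusion.** The point holds as one of efficiency and clarity. The plan rules out baseline adjustment in its main analysis and leaves two tests, with different summaries, for one primary outcome. Under log-normal proteinuria with equal log SDs, adjustment on the log scale adds about 17 points of power at ρ = 0.3 (18 against ANOVA alone), about 8 at ρ = 0.5, and nothing material from 0.7 upward. With a wider month-6 spread it adds 2 to 7 points. No scenario examined showed a loss. The 6% to 7% type I error arises only if both tests are run and the better one is reported, which the article does not say will happen. The change is worth making, but the existing analysis is not wrong.

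**What to change.** Name one primary model in Statistical analysis: ANCOVA of log month-6 24-h proteinuria on treatment arm and log baseline proteinuria as a continuous covariate. Report the geometric mean ratio of each dose to placebo with its 95% CI, and convert it to a percentage reduction. Keep Kruskal-Wallis on percentage change as a sensitivity analysis, and confine the normality test to descriptive choices.

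The cost is a change of wording; it needs no extra patients, visits or measurements. The small downside is that the reported summary becomes a geometric mean ratio instead of a mean or median percentage change, so Outcome measurements should be reworded to match.

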**Table 1 Tab1:**
[figure not shown]
Schedule of recruitment, interventions, and assessments

^a^Items include urea, creatinine, total bilirubin, serum glutamic pyruvic transaminase, serum glutamic-oxaloacetic transaminase, alkaline phosphatase, sodium, potassium, calcium, phosphorus, total protein, albumin, and uric acid

^b^Items include urea, creatinine, sodium, and potassium

^c^Items include Gd-IgA1 and anti-Gd-IgA1(IgG/IgA)

*Abbreviation*: *HCG*, human chorionic gonadotropin

The primary outcome measures will be determined by the percentage change in proteinuria in the three groups after 6 months of intervention. The secondary outcome measures will be the changes in urinary protein creatinine ratio and estimated glomerular filtration rate (eGFR) from baseline after 1, 3, and 6 months of intervention, and the changes in serum galactose-deficient IgA1 (Gd-IgA1) and anti-Gd-IgA1 levels in patients will also be observed. We will stratify the risk of progression of the IgA patients and retrospectively evaluate the effect of ART on the proteinuria levels in IgA patients with different progression risks. Safety assessment of ART will be carried out throughout the study. The study protocol was approved by the Ethics Committee of Dongzhimen Hospital Affiliated with Beijing University of Chinese Medicine (Number: DZMEC-KY-2020-30) and registered in the Chinese Clinical Trial Registry (ChiCTR) (Number: ChiCTR2000038104).

This protocol has been reported according to the Standard Protocol Items: Recommendations for Interventional Trials (SPIRIT) 2013 statement [23]. The SPIRIT checklist is listed in Supplement Table 1. A complete list of clinic hospitals where data will be collected is available in Supplement Table 2.

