### Participant recruitment

#### Inclusion criteria

The inclusion criteria for this study are (1) ages 18–75, (2) primary IgA nephropathy confirmed by renal biopsy, (3) persistent proteinuria ≥1.0 g/day after receiving adequate RAAS blocker treatment (proteinuria ≥1.0 g/day at visit 1 and visit 3), and (4) eGFR ≥30 ml/min per 1.73 m^2^ calculated by the Chronic Kidney Disease Epidemiology Collaboration (CKD-EPI) equation.

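### The 3 g/day baseline-proteinuria cut leaves only about 4 to 5 patients per arm above it; baseline proteinuria should be a continuous effect modifier, with the cut kept for description

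*Protocol article*

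**What the plan says.** The Statistical analysis section of the protocol article plans an unadjusted initial analysis. For the secondary analysis it states that "we will adjust for confounders for subgroup analyses, such as baseline proteinuria (3 g/day"), and goes on to eGFR at 45, systolic pressure at 140 mmHg, the MEST-C classification and an international risk-prediction score. One two-sided 0.05 threshold is stated for the whole plan.

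The aim behind this appears in the Study design section, in the text after Table 1. There the investigators will stratify patients by risk of progression and "retrospectively evaluate the effect of ART on the proteinuria levels in IgA patients with different progression risks".

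The figures that determine the size of the proteinuria subgroups are elsewhere in the article. Under Sample size, "the average baseline proteinuria was 2.0±0.8 g/day" and "we plan to enroll 120 participants (40 in each group) in the study". Under Inclusion criteria, patients need "persistent proteinuria ≥1.0 g/day after receiving adequate RAAS blocker treatment". No upper limit on proteinuria is set. The article gives no expected number of patients above 3 g/day.

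**The concern.** A subgroup cut is useful only if enough patients fall on each side of it. This one lies far from the centre of the population the protocol itself expects, so one side will be nearly empty.

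Two things are at stake. First, the estimate above 3 g/day will be too imprecise to inform anyone. Second, the pair of results may be misread. If the drug works equally well on both sides, the large subgroup can reach significance while the small one does not, and that could be taken as lack of benefit in the patients with the heaviest proteinuria.

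The sentence is also unclear about what is being done. Adjusting the overall treatment effect for baseline factors and asking whether the effect differs by baseline factor are separate analyses. The wording merges them, so a programmer could implement either.

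**Working it through.** **Inputs.** Baseline mean 2.0 and SD 0.8 g/day, 40 enrolled and 36 evaluable per arm, 90% power, type I error 0.05 (Sample size); two-sided testing and the 3 g/day cut (Statistical analysis); entry at 1.0 g/day or more (Inclusion criteria). The shape of the distribution is not given and is assumed.

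**The plan's own figures.**
- Dropout: 36 / (1 − 0.10) = 40 per arm, as stated.
- The 36 per arm is roughly recovered for a 1:1 comparison of a 0.5 g/day difference with SD 0.5 on ART and an assumed 0.8 on placebo: (1.960 + 1.282)² × (0.8² + 0.5²) / 0.5² = 10.51 × 0.89 / 0.25 = 37.4. Power at 36 per arm is 88.9%.

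**Share above the cut.** z = (3 − 2.0) / 0.8 = 1.25.

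| Assumed shape | Share above 3 g/day | Per arm of 40 |
|---|---|---|
| Normal (2.0, 0.8) | 10.6% | 4.2 |
| Same, truncated at 1.0: 0.1056 / 0.8944 | 11.8% | 4.7 |
| Lognormal, mean 2.0, SD 0.8 | 10.7% | 4.3 |
| Same lognormal, truncated at 1.0 | 11.3% | 4.5 |
| Truncated normal refitted to mean 2.0, SD 0.8 | 12.0% | 4.8 |
| Gamma shifted to start at 1.0, same mean and SD | 10.9% | 4.4 |
| Lognormal shifted to start at 1.0, same mean and SD | 9.1% | 3.6 |

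The first two rows give 0.1056 × 120 = 12.7 and 0.1181 × 120 = 14.2, so about 13 to 14 patients in the trial. Among 36 evaluable per arm they give 3.8 to 4.3.

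**Chance variation.** Under a binomial with n = 40, the 95% range for one arm is 1 to 8 (p = 0.106) or 1 to 9 (p = 0.118). The chance that a given arm has two or fewer is 0.191 or 0.133. For at least one of three arms it is 1 − 0.809³ = 47% or 1 − 0.867³ = 35%.

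**Precision, free of the measurement scale.** With equal spread on both sides, interval width goes with 1/√n.
- Above against below the cut: √(0.894 / 0.106) = 2.9, or √(0.882 / 0.118) = 2.7 times as wide.
- With 90% power at two-sided 0.05, the planned effect equals 1.960 + 1.282 = 3.242 standard errors. The whole-trial 95% half-width is then 1.960 / 3.242 = 0.60 of the planned effect.
- Above the cut: 0.605 / √0.106 = 1.86, or 0.605 / √0.118 = 1.76 times the planned effect.
- Below the cut: 0.605 / √0.894 = 0.605 / √0.882 = 0.64 of the planned effect.

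Suppose both subgroups showed exactly the planned effect. The interval below the cut would exclude zero; the one above would run from well below zero to more than twice the planned effect. This takes the stated 90% at face value and assumes the same effect and spread on both sides on the analysis scale. A t quantile would widen the upper interval further.

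**Information lost by cutting.** If the treatment effect changes linearly with a normally distributed baseline, a cut keeps φ(z)² / [p(1 − p)] of the information about that trend. At z = 1.25 this is 0.1826² / (0.1056 × 0.8944) = 0.35; at p = 0.118 it is 0.38. A median split keeps 0.64 and the continuous value keeps all of it.

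**The case against.** Much of the case on the other side stands, and it limits how far the point goes.

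- **Missing interaction test.** A reader might count its absence as an error. The document is a journal article, and the model for a secondary subgroup analysis is commonly left to the full protocol or analysis plan, neither of which is shown. The text does not exclude an interaction term. Separate tests within each subgroup at the 0.05 level are likewise an inference, not something the article states.
- **The effect-by-risk question as a whole.** A reader might conclude that it cannot be answered. The Study design text does not tie progression risk to 3 g/day. Four other factors are listed, including a risk-prediction score that addresses progression risk directly, and their subgroup sizes cannot be computed from the article.
- **Power in g/day.** It is tempting to compute power above the cut for a fixed 0.5 g/day effect. The primary outcome is percentage change, so a 25% reduction is a larger absolute change in patients with heavier proteinuria, and their spread may be larger too. Such figures do not describe this endpoint and are not relied on here.
- **False-positive rate.** A rate across all subgroups would need the number of levels and the prevalence of each factor. The article gives neither.
- **The planning figures.** They come from hydroxychloroquine studies, and there is no upper entry limit, so the enrolled share above 3 g/day may differ. Simple truncation at 1.0 g/day also raises the mean to 2.0 + 0.8 × 0.1826 / 0.8944 = 2.16. The version refitted to 2.0±0.8 nevertheless gives 12.0%, so the conclusion does not change.
- **Fixed cuts.** Stating cuts in advance is legitimate and guards against choosing them from the data. That defends having a stated rule; it does not make a subgroup of 4 to 5 per arm informative.

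**Conclusion.** The concern holds in a limited form. On the protocol's own planning figures, the stated cut puts about 11% of patients above 3 g/day: roughly 4 to 5 per arm, with 3.6 to 4.8 across the shapes tried. That subgroup cannot give a useful estimate, and a contrast in significance between the two sides would mainly reflect their unequal size. The sentence also merges covariate adjustment with effect modification and should separate them.

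This rests on enrolled patients resembling the planning figures and on an approximately normal or similar moderately skewed distribution. It concerns one of five listed factors, in a secondary analysis of a trial that its Discussion calls proof-of-concept. The primary result is unaffected. Severity: minor.

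**What to change.** Split the sentence into two statements.

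1. **Covariate adjustment:** name the baseline factors used to adjust the overall treatment effect.
2. **Effect modification:** for example, 'Whether the effect of ART varies with baseline proteinuria will be explored in a model for the month-6 outcome containing treatment, log baseline proteinuria and their product. The ART-placebo difference will be reported with its 95% confidence interval at 1.5, 2 and 3 g/day. Effect modification will be judged from the product term and is exploratory. Results either side of 3 g/day will be shown for description only.'

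The same form suits eGFR, systolic pressure and the risk score.

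The cost is a change of wording and slightly different SAS code, with no new data, visits or patients. The model assumes a roughly linear trend in log baseline, which can be checked with a plot or a curvature term. The interval at 3 g/day will still be wide because few patients lie near it, and power for effect modification remains limited at 120 patients. The gain is that every patient contributes to the estimate and the result no longer depends on how few fall above the cut.
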